## Abstract

**Introduction:**

The incidence of head and neck cancer (HNC) in the UK is rising, with an average of 31 people diagnosed daily. Patients affected by HNC suffer significant short-term and long-term post-treatment morbidity as a result of dysphagia, which affects daily functioning and quality of life (QOL). Pretreatment swallowing exercises may provide additional benefit over standard rehabilitation in managing dysphagia after primary HNC treatments, but uncertainty about their effectiveness persists. This study was preceded by an intervention development phase to produce an optimised swallowing intervention package (SIP). The aim of the current study is to assess the feasibility of this new intervention and research processes within a National Health Service (NHS) setting.

**Method and analysis:**

A two-arm non-blinded randomised controlled feasibility study will be carried out at one tertiary referral NHS centre providing specialist services in HNC. Patients newly diagnosed with stage III and IV disease undergoing planned surgery and/or chemoradiation treatments will be eligible. The SIP will be delivered pre treatment, and a range of swallowing-related and QOL measures will be collected at baseline, 1, 3 and 6 months post-treatment. Outcomes will test the feasibility of a future randomised controlled trial (RCT), detailing rate of recruitment and patient acceptance to participation and randomisation. Salient information relating to protocol implementation will be collated and study material such as the case report form will be tested. A range of candidate outcome measures will be examined for suitability in a larger RCT.

**Ethics and dissemination:**

Ethical approval was obtained from an NHS Research Ethics Committee. Findings will be published open access in a peer-reviewed journal, and presented at relevant conferences and research meetings.

**Trial registration number:**

ISRCTN40215425; Pre-results.

Strengths and limitations of this studyUse of a randomised controlled trial design to minimise bias and differences between groups.Study design incorporates prior qualitative work to optimise adherence to the intervention.Method includes consultation with clinicians involved in usual care to devise a usual care protocol to facilitate consistency.Limited to one hospital site.Patients and clinicians are not blinded to randomisation allocation.

## Introduction

### Background

Incidence of head and neck cancer (HNC) in the UK is rising^1^ with an average of 31 people receiving a new diagnosis daily.^2^ This increase is primarily attributed to the rise in human papilloma virus (HPV)-related oropharyngeal cancer.^3^ Individuals with HPV-induced malignancy are often much younger than those with cancers induced by smoking and alcohol, and often otherwise healthy and in active employment. Reducing the morbidity of cancer treatments is a priority for the NHS Cancer Reform Strategy^4^ and the Macmillan Living with and Beyond Cancer Programme.^5^ Patients affected by HNC suffer significant short-term and long-term post-treatment morbidity as a result of dysphagia, which affects daily functioning and quality of life (QOL). Swallowing difficulties may arise secondary to the presence of tumours in the mouth and throat, 6 from damage or resection of swallowing-related soft tissues and nerves during surgical intervention^7^ and from the side effects and long-term tissue damage following chemoradiation.^8^ Swallowing interventions that may ameliorate the problems associated with eating and drinking after primary HNC treatments (surgery, chemoradiotherapy) are an important part of the care delivered to patients diagnosed with HNC.^9^

### Current UK practice for managing dysphagia in HNC

Traditionally, patients would have seen a speech and language therapist (SLT) following their cancer treatment for rehabilitation of their swallowing and communication difficulties. A gradual shift in practice occurred following publication of the National Institute for Health and Care Excellence (NICE) Improving Outcomes Guidance,^10^ which recommend that patients should also see an SLT *prior* to their treatment to inform them of the *likely* impact to their swallowing and speech function. This information giving is also viewed as a necessary part of the process of informed consent. In support, an emerging number of functional outcome studies have indicated that swallow function pre treatment could be a strong predictor of long-term swallow function post-treatment.^11–13^

Implementation of the NICE recommendation is currently variable. In some centres, patients are provided with brief information by the SLT at the time of seeing their medical consultant in a multidisciplinary clinic setting. In other centres, separate SLT consultations take place, which include documentation of baseline functional measures for swallowing and communication, as well as advice on diet modification and the recommendation to start a general protocol of swallowing exercises. The latest report from the UK National Database of Head and Neck Oncology (DAHNO)^14^ indicated that only 29% of patients with HNC in England and Wales were recorded as having a pretreatment SLT consultation. Given the clinical and financial resource implications of a separate pretreatment SLT consultation, implementation will likely only increase if there is clear specification as to the optimal content of the consultation, together with evidence supporting its benefit on patients' outcomes. Aside from information giving, there is a need to define what interventions administered *before* treatment (prehabilitation) may improve patient experience and/or post-treatment function.

### The role and context of pretreatment swallowing exercises

The physiological rationale for prophylactic swallowing exercises has been previously described in the literature. Strength-based exercises and/or range of movement exercises aimed at the swallowing musculature may prevent muscle atrophy and reduce or delay the impact of radiation-induced fibrosis.^15–18^ Preconditioning through exercises has been reported to be helpful in other types of surgery.^19^ Swallowing is described as a ‘suboptimal activity’^20^ meaning that it can be adequate for the purpose of obtaining oral nutrition even when not at maximal physiological functioning. While it seems intuitive that pretreatment swallowing exercises should be helpful in increasing physiological reserve, reducing disuse atrophy and possibly delaying the onset of fibrosis, uncertainty about its effectiveness in improving swallowing for patients with HNC persists.^21^ Few randomised clinical trials have attempted to address this knowledge gap, with mixed results.^17^
^22–28^ Trials evaluating the effects of pretreatment swallowing exercises suffer limitations in study design, and the lack of consistent outcome measures across studies is problematic.^21^ Uncertainty also remains as to the optimal type and frequency of exercises although such considerations are less relevant to tailored interventions guided by prior physiological assessment. The practice of providing prophylactic swallowing exercises varies among UK clinicians,^29^ and to date there is no published UK data supporting the effectiveness of pretreatment swallowing exercise interventions in the HNC population.^21^ Any pretreatment intervention package will need to address often poor patient adherence to swallowing exercises.^22^
^24^
^30^ Improved adherence may be achieved by facilitating a change in patient behaviour. A new intervention will also need to be compatible with the broader cancer care pathway as detailed in figure 1.

**Figure 1 BMJOPEN2016014167F1:**
[figure not shown]
Pathway of care for patients with head and neck cancer.

### Development of a tailored pretreatment swallowing intervention package (SIP)

In preparation for the feasibility study described in this manuscript, an optimised SIP was developed by the researchers, guided by the methodology proposed by the Medical Research Council (MRC) for devising complex interventions incorporating multiple components that may interact in producing outcomes.^31^ The scope of the current work relates to the development and feasibility testing phases of a complex intervention, but the framework also includes evaluation and implementation phases with updated guidance that incorporates a *process* evaluation.^32^ We briefly describe the development work below.

Recognising the poor patient adherence reported in previous studies of swallowing exercises,^22^
^24^
^30^ we paid specific attention to optimising patient adherence during the development phase by drawing on theoretical frameworks and tools (The Behaviour Change Wheel, Behaviour Change Technique Taxonomy v1) from the field of behavioural science.^33^
^34^

The new SIP—Swallowing Intervention Package: Self-Monitoring, Assessment, Rehabilitation Training (SIP SMART) was devised using current best evidence of swallowing assessment,^35^ as well as insights from our earlier studies exploring the behavioural dimensions of this complex intervention; a systematic review of the literature^36^ and a patient interview study *(submitted manuscript).*

In our systematic review of behavioural swallowing intervention studies,^36^ we used a published taxonomy (BCTTv1)^33^ of 93 hierarchically organised behaviour change techniques (BCTs), to identify the BCTs reported in the literature. BCTs may be defined as the smallest active ingredient of an intervention that may bring about a change in behaviour, for example, *demonstration of the behaviour* or *self-monitoring of the behaviour*. We surmised that the BCTs that were more frequently associated with successful interventions were more likely to be successful in future interventions.

We also carried out semistructured interviews with a group of patients (n=13) who had completed treatment for HNC to obtain their views and experiences of swallowing rehabilitation exercises, and in addition obtained feedback from respondents about the potential use of video animations (Dysphagia App, Northern Speech Services, USA) as an educational tool in explaining the basic mechanics of swallowing. The barriers and facilitators to exercise adherence revealed in our qualitative study informed our behavioural analysis and the subsequent selection of BCTs for the SIP SMART intervention.

We ensured that the new SIP would meet mandatory guidelines^10^ for information provision and informed consent, and that it could feasibly be incorporated within the existing cancer pathway for patients with HNC. The new SIP was discussed and refined by clinician (Royal College of Speech and Language Therapist expert clinician group (RCSLT)) and patient (patient–public involvement group (PPI)) stakeholder groups. Intervention manuals were produced for the new intervention and usual care in collaboration with the stakeholder groups. Figure 2 is a schematic diagram illustrating an overview of this process and how it links to the MRC complex interventions framework.

**Figure 2 BMJOPEN2016014167F2:**
[figure not shown]
Key stages of the *MRC complex interventions framework that informed the development and preliminary testing of the SIP SMART intervention. *Source: Craig *et al*, BMJ;2008. MRC, Medical Research Council; SIP SMART, Swallowing Intervention Package: Self-Monitoring, Assessment, Rehabilitation Training.

Although another complementary non-randomised UK trial of pretreatment swallowing intervention is planned,^37^ our SIP SMART trial is unique as it is based on an optimised pretreatment intervention using tailored exercises selected after physiological assessment of swallowing, and is directly informed by theoretically derived BCTs. Furthermore, comprehensive evaluation of a new SIP is likely best performed using a randomised controlled trial (RCT) design. Given the uniqueness of our SIP and proposed future RCT evaluation, a feasibility study was deemed imperative to ascertain viability within a NHS context, and to identify and address potential barriers to future roll out on a larger scale.

In particular, the aims of this feasibility study are as follows:
Assess the rate of recruitment of eligible participants and identify any specific barriers to recruitment.Determine the acceptability of randomisation, and the randomisation procedure to patients and the clinical care team.Determine retention and attrition over the time course of the study.Evaluate the ease of protocol implementation, including research processes, and identify barriers in the clinical setting.Evaluate a range of potential outcome measures, including the ease and completeness of data collection across various time points.Determine concordance between potential outcome measures and define the most suitable primary outcome for the definitive study.Collect data to inform future sample size calculation.

## Methods and analysis

### Study design

This study forms the preliminary testing phase described within the MRC complex interventions framework. Following on from our development work, we will conduct a two-arm parallel group non-blinded randomised controlled feasibility study. The SPIRIT^38^ (Standard Protocol Items for Randomised Interventional Trials) checklist of was used to inform the content of this protocol.

### Study population, setting and recruitment plan

The study will take place at a single NHS hospital site (Head and Neck Cancer Centre) with a catchment population of 1.5 million. The study sample will be drawn from the population of patients with newly diagnosed HNC referred to the cancer centre, and discussed at the weekly multidisciplinary team (MDT) meeting. Potential patients for the study (based on diagnosis) will be identified during the meeting by the researcher (RG), research nurse or other members of the MDT. The research team will ensure that the treating consultant is aware of potentially eligible patients so that he/she may introduce the study during the consultation with the patient if appropriate. For this feasibility study, sample size was determined pragmatically using the general guidance suggested by Lancaster and colleagues^39^ who recommend that n of 30 is sufficient to estimate key parameters in a feasibility study. Based on a conservative annual referral of ∼70 newly diagnosed stage III and stage IV patients with HNC to the Head and Neck Centre, we estimated that it will take about 9 months to recruit a total of 32 patients to this study based on recruiting 60% of eligible patients. Eligibility criteria for inclusion in the study are listed in box 1.
Box 1Inclusion and Exclusion CriteriaInclusion:
Patients with newly diagnosed stage III and stage IV head and neck cancer.Discussed at the head and neck MDT and planned for treatment via surgery and/or chemoradiotherapy or combinations thereof.Able to provide informed consent.Proficiency in English satisfactory to participate/engage in the intervention.Aged 18 and above.Exclusion:
Patients with previous head and neck cancer treatment.Patients who are mid treatment or those receiving palliation.Patients who are to be treated solely by non-standard treatment that is not surgery, radiotherapy, chemoradiotherapy or combinations thereof. Patients treated by chemotherapy, brachytherapy and photodynamic therapy alone will be ineligible.Patients who are planned for a total laryngectomy.Patients who are considered vulnerable or unable to provide informed consent.Patients with brain tumours and other primary sites not within head and neck.

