### Prescreening/screening

All patients who meet the clinical eligibility criteria identified at each MDT meeting will be recorded on the study screening log by the researcher or research nurse. Screening will take place at the outpatient clinic consultation when treatment options are discussed by the surgeon/oncologist. The researcher/clinician will attend the consultations for eligible patients. If appropriate at this stage, the purpose of the study will be explained and patients will be given the patient information leaflet to take away. Most patients will be booked for repeat visits to the head and neck clinic prior to finalising their treatment plan. Due consideration will be given to ensuring that the study information is discussed at an appropriate time after the diagnosis. Patients will be given a minimum of 24 hours after receiving the patient information sheet before a mutually agreed time is arranged to answer any further questions to assist patients in deciding about whether to participate. The time frame was chosen because most patients return to the hospital for other tests the day after their clinic visit. This offers an opportunity to answer questions in person and obtain signed consent if appropriate. Patients will be reassured that participation is voluntary with the freedom to withdraw at any stage, and that participation in the study will not affect or delay their main treatment.

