### Analysis

We will use mainly descriptive analysis and summary statistics to address our aims. Study screening and enrolment logs will be used in determining the rate of recruitment into the study. All qualitative information (researcher diary), minutes of study-related discussions and meetings will be imported into NVIVO 10, a software database to facilitate the organisation and thematic coding of qualitative or textual data. The researcher is in a unique position of being embedded within the clinical team, and therefore able to make observations over the duration of the study in a naturalistic manner. This approach to process analysis arguably may provide more useful information than the use of post hoc focus groups and interviews that rely on participant memory and may be removed from context.^48^ Observing and collecting information in this way also means that the researcher can observe the interplay of other factors (eg, multiple studies competing for the same patient group, prevailing views of the treating consultant about the value of the proposed intervention and how busy the clinic is) that may reveal vital information about the barriers and facilitators to recruitment.

We will also report on the practicality of implementing the protocol, for example, obtaining timeslots for videofluoroscopy; average time taken for the recruitment and consent process; utility of the chosen randomisation method and suitability of the study-specific forms including the CRF. This information will be used to optimise components of the protocol and study process in preparation for a larger trial.

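### Acceptance of randomisation is a condition for proceeding, but only patients who accepted it and stayed to 6 months can answer the questionnaire that decides it

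*Protocol article*

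**What the plan says.** The list of aims at the end of the Introduction opens with "Assess the rate of recruitment of eligible participants and identify any specific barriers to recruitment". The second aim is to find out whether randomisation is acceptable to patients and to the clinical team.

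On acceptability, the Analysis section says that a previously developed questionnaire will determine it. Table 1 (Baseline and follow-up outcome measures) schedules that questionnaire at 6 months and at no other time point. Criteria for success then makes generally positive views on participation and randomisation, as shown by the questionnaire, one of the conditions for going on to a definitive trial.

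On the route into the study, the section on study population, setting and recruitment plan says the treating consultant is made aware of potentially eligible patients "so that he/she may introduce the study during the consultation with the patient if appropriate". Prescreening/screening puts every clinically eligible patient from the MDT meeting on the screening log. Enrolment/consent puts consented patients on the enrolment log. The one use stated for the two logs is in Analysis: "Study screening and enrolment logs will be used in determining the rate of recruitment into the study". Barriers to recruitment are to come from the researcher's diary, observations made while embedded in the clinical team, and minutes of study discussions and meetings.

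**The concern.** A question about whether patients accept randomisation is being put only to those who did. Anyone who refused because of randomisation is gone before the questionnaire exists, and anyone who leaves before 6 months is also lost to it. A favourable result is therefore likely almost by construction, yet it counts as evidence for a go decision.

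The recruitment figure does not fill the gap. A patient can be on the screening log but not on the enrolment log because the study was never raised, because the approach was put off until too late, or because the patient said no. Refusal may itself concern randomisation, the extra consultation, the videofluoroscopy, another trial or something else. One ratio of enrolled to eligible combines all of these. They call for different changes to a definitive trial, and the article's Discussion cites a UK trial in this population that recruited only 23% of eligible patients as a reason why this feasibility work is needed.

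**Working it through.** **1. Reproduce the plan's recruitment figure.** The inputs are in the section on study population, setting and recruitment plan: "Based on a conservative annual referral of ∼70 newly diagnosed stage III and stage IV patients with HNC", and "it will take about 9 months to recruit a total of 32 patients to this study based on recruiting 60% of eligible patients".

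- Eligible per month: 70 / 12 = 5.83.
- Recruited in 9 months: 70 × 9/12 × 0.60 = 31.5, against 32 stated.
- Time to 32: 32 / (5.83 × 0.60) = 9.14 months, against about 9 stated.

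The figure reproduces.

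**2. Patients who are not enrolled.** Eligible patients needed: 32 / 0.60 = 53.3. Not enrolled: 53.3 − 32 = 21.3, or 40% of those eligible.

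**3. What the 60% can conceal.** The share of eligible patients who are approached is not given, so I assume a share *f* between 60% and 100%. Approached = 53.3 × *f*; uptake among those approached = 0.60 / *f*; never approached = 53.3 × (1 − *f*); declined = 53.3 × *f* − 32.

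| Assumed share approached | Approached | Uptake among approached | Never approached | Declined |
|---|---|---|---|---|
| 100% | 53.3 | 60% | 0 | 21.3 |
| 90% | 48.0 | 67% | 5.3 | 16.0 |
| 80% | 42.7 | 75% | 10.7 | 10.7 |
| 70% | 37.3 | 86% | 16.0 | 5.3 |
| 60% | 32.0 | 100% | 21.3 | 0 |

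Every row gives the same enrolled/eligible figure.

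**4. Who can answer the acceptability questionnaire.** The sequence is eligible, approached, consented, randomised, still in follow-up at 6 months, then questionnaire. At most 32 patients reach the last step, and none of the 21.3 can. To illustrate, assume all 53.3 are approached and all 32 enrolled patients respond favourably. The questionnaire then reads 100% whether none of the 21.3 refused because of randomisation (acceptance of randomisation among those approached 53.3 / 53.3 = 100%) or all of them did (32 / 53.3 = 60%). The criterion gives the same answer in both cases.

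**5. Whether the cause is likely to be needed.** Criteria for success asks for an average of four patients a month, which is 4 / 5.83 = 69% of eligible patients. The planning assumptions give 5.83 × 0.60 = 3.5 a month. A shortfall against that criterion is quite possible, and explaining it would require knowing whether access or refusal was responsible.

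**The case against.** A reader might infer more than the article supports, in four ways.

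- **That the study cannot tell patients who were never offered it from those who declined.** The article does not list the fields of the screening log, the forms are not reproduced, and the trial flow chart is not shown. Approach status and decline reason are ordinary form-level detail that an article leaves out. The researcher/clinician also attends eligible patients' consultations, so the information is within reach. Silence about the log is not evidence that it lacks these fields.
- **That staff decide whether an eligible patient is told at all.** The wording in Prescreening/screening, "If appropriate at this stage, the purpose of the study will be explained", reads mainly as a matter of timing. Repeat clinic visits follow, and the same section adds: "Due consideration will be given to ensuring that the study information is discussed at an appropriate time after the diagnosis". Only the sentence on the consultant leaves the question of whether open.
- **That barriers rest on the recruiter's diary alone.** Analysis also names minutes of discussions and meetings. It sets out to observe competing studies, consultants' views and clinic workload, and it gives a reason for preferring embedded observation to later interviews.
- **That patients who decline have no bearing on the go decision.** They lower the recruitment rate, which is a criterion in its own right.

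All four objections stand. None removes the core point. The instrument for acceptability, its single 6-month time point and its role as a progression criterion are all fixed in the text, and together they leave out everyone who refused. The recruitment-rate criterion registers a refusal without its cause. The examples of barriers given in Analysis lie on the clinician and clinic side; a patient's own reason for refusing is not among them.

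**Conclusion.** The point holds in this form: the progression criterion on acceptance of randomisation is judged on a group selected for having accepted it and for having stayed to 6 months, so it is biased towards a positive result. The documents do not allow the size of that bias to be estimated. What they do show is that about 21 of about 53 eligible patients (40%) would fall outside the assessment if the planned 60% is met.

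The point about the logs is lesser and conditional. As described, they yield one ratio, compatible with uptake among those approached anywhere from 60% to 100%. That range rests on the assumption that 60% to 100% of eligible patients are approached, and on the planned 60% being achieved. If the log form already records approach, decision and reason, what remains is to say so and to use those data for the first two aims and for the criterion.

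This is worth changing before recruitment starts. It alters what the study can conclude on those aims, although it does not affect its conduct or its recruitment target.

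**What to change.** 1. On the existing screening log, record for each eligible patient: approached yes/no, with the reason if not; the decision; and, for those who decline, a voluntary reason from a short list that includes unwillingness to be randomised, extra appointments, videofluoroscopy, another trial, and other. If the form already has these fields, state it.
2. Report approached/eligible and consented/approached with 95% intervals, and tabulate the decline reasons, including the number who gave none. Use these with the diary and minutes for the barriers aim. Precision will be modest: if all 53 were approached and 60% consented, the simple interval is 0.60 ± 1.96 × √(0.60 × 0.40 / 53) = 0.60 ± 0.13, or about 47% to 73%.
3. Amend Criteria for success so that acceptance of randomisation is judged on the questionnaire together with the number who declined because of randomisation, out of those approached.

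The cost is a few columns on a log already kept by the researcher or research nurse, and one table. No extra visits or staff are needed. The limitation is that some patients will decline without giving a reason, so the count of refusals due to randomisation will be a minimum.

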### Criteria for success

This study will be viewed as feasible to proceed to a definitive trial if:
a suitable outcome measure is determined, and sample size estimated;recruitment rate into the trial reaches an average of four patients a month;patients report generally positive views about participation and acceptance to randomisation as determined by questionnaire evaluation;patients in the intervention group are more adherent than those in usual care, with at least 35% of intervention group patients reporting satisfactory to good adherence to exercises.

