## Discussion

To the best of our knowledge, this is the first randomised UK study of a behavioural swallowing exercise intervention for patients with HNC registered on the trials database. By undertaking a feasibility study and identifying key uncertainties, any future study may be optimised to make best use of resources.^50^ This study follows earlier work on intervention development bringing together expertise from different fields including clinical dysphagia management and behaviour change. It benefits from the use of newer paradigms in health research including the use of consultative and consensus meetings to devise a treatment manual to specify the content of *usual care*, a common omission when reporting such interventions.^51^ It is likely to provide a rich source of information about how readily patients with a new diagnosis of HNC will accept and participate in a self-management-type intervention. It will also provide a preliminary indication of the recruitment potential for rehabilitation therapy trials for this population. A recent UK study^52^ that randomised HNC patients to either a pretreatment gastrostomy tube or a nasogastric tube reported recruiting only 23% of eligible patients, highlighting the importance of this feasibility work. It is well known that the treatment of HNC involves a complex care pathway with multiple disciplines being involved, particularly at the pretreatment stage. The feasibility of undertaking a clinical trial at this point in the patient pathway is compounded by the challenges of approaching patients to participate in a trial shortly after receiving a cancer diagnosis. Insights from this study may therefore have more widespread relevance for future studies of this population.

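### The recruitment criterion for going ahead is a monthly head count only; it mixes uptake with this centre's referral volume, and at the plan's own volume it requires 69% uptake against a planned 60%.

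*Protocol article*

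**What the plan says.** The first aim, at the end of the Introduction, is to "Assess the rate of recruitment of eligible participants and identify any specific barriers to recruitment". No unit is attached to that rate.

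The forecast is in Study population, setting and recruitment plan. It starts "Based on a conservative annual referral of ∼70 newly diagnosed stage III and stage IV patients with HNC", and concludes that "it will take about 9 months to recruit a total of 32 patients", "based on recruiting 60% of eligible patients".

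Under Prescreening/screening, every patient found clinically eligible at the weekly team meeting goes on the screening log. The Analysis section then states: "Study screening and enrolment logs will be used in determining the rate of recruitment into the study".

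Criteria for success has one recruitment item: "recruitment rate into the trial reaches an average of four patients a month". None of the other items (outcome measure and sample size, participants' views, adherence) sets a minimum share of eligible patients.

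The Discussion mentions a UK feeding-tube trial in head and neck cancer that "reported recruiting only 23% of eligible patients", as a reason why feasibility work is needed.

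**The concern.** The plan's uncertain quantity is how many eligible patients will agree to join soon after a cancer diagnosis. It assumes 60% and points to a trial that achieved far less. The decision rule does not test this quantity. It tests a product, uptake times the number of eligible patients arriving at one hospital, so the same verdict can come from very different levels of acceptance.

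Two errors follow. A study with the planned uptake can fail because the volume is only what was forecast. A study with lower uptake than planned can pass because the volume was higher. Either would misinform the decision on a definitive trial, which would run in hospitals with other volumes. To forecast accrual there, one needs uptake and volume separately, and this centre's count gives only their product.

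**Working it through.** **Inputs.** Volume V of about 70 a year, uptake u = 60%, target 32 patients in about 9 months (recruitment plan); threshold of 4 a month (Criteria for success); 23% comparison (Discussion).

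**1. Reproduce the forecast.** Monthly accrual = V × u / 12 = 70 × 0.60 / 12 = 3.5. Time to 32 patients = 32 / 3.5 = 9.1 months, and nine months yields 3.5 × 9 = 31.5 patients. The stated figures reproduce.

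**2. Uptake that the threshold requires.** Four a month is 48 a year, so required u = 48 / V.

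| Eligible patients a year | Uptake needed for 4 a month |
|---|---|
| 60 | 80% |
| 70 (plan) | 69% |
| 80 | 60% |
| 100 | 48% |
| 120 | 40% |

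The planned 60% meets the rule only if volume reaches 80 a year.

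**3. Good uptake failing.** At the plan's own figures, expected accrual is 3.5 a month against a threshold of 4. Four a month over nine months is 36 patients, and 31.5 are expected. If accrual is Poisson (my assumption), the chance of at least 36 is about 23%. At 50 a year, even 80% uptake gives 50 × 0.80 / 12 = 3.3 a month and misses.

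The forecast applies 60% to all 70 referrals. If only 70% to 90% of them are eligible (assumption), the denominator is 49 to 63 a year and the rule requires 48 / 49 = 98% down to 48 / 63 = 76%.

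**4. Poor uptake passing.** At 70 a year, 23% uptake gives 70 × 0.23 / 12 = 1.3 a month and fails clearly. It would pass only at 48 / 0.23, about 209 a year. More moderate shortfalls pass sooner: 48% at 100 a year, 40% at 120.

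**5. Can uptake be estimated usefully?** Nine months at 70 a year is 70 × 9 / 12 = 52.5, about 53 eligible patients. With 32 of 53 enrolled, uptake is 60%, exact 95% interval 46.0% to 73.5%. That is wide, but informative.

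**6. Would 23% serve as a pass mark?** Suppose the rule were a lower 95% limit above 23%. Then 32/100 = 32% passes (exact interval 23.0% to 42.1%), as does 19/53 = 36% (lower limit 23.1%). At 70 a year, 32% uptake is 70 × 0.32 / 12 = 1.9 a month, about 17 months for 32 patients. Such a rule would accept little more than half the planned uptake.

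**The case against.** The strongest reply is that uptake is already captured. Eligible patients are logged, the recruitment rate is to be worked out from both logs, and barriers to recruitment are studied. This stands as far as data and reporting go: nothing is lost, and the defect is confined to the decision rule.

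A second reply is that a monthly rate is what determines whether a trial can finish, and that a share alone could approve a site with too few eligible patients. This also stands, and is why the count should be kept.

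A third is that acceptance has its own criterion. That criterion rests on a questionnaire that Table 1 schedules at 6 months, so it reaches enrolled participants and not those who declined.

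A reader might also infer that the aim, the forecast and the benchmark are all shares of eligible patients and that only the rule departs from them. The text does not go that far. The aim has no unit, the forecast ends as a count over time, and the 23% is background from another trial, not a target here.

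Nor do the documents show that the rule would hide very poor uptake at this centre. One could build a much larger volume from the national incidence and the catchment of 1.5 million, but that needs outside assumptions about population, stage and referral and ignores the exclusion criteria. The only site figure given is about 70.

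**Conclusion.** The concern holds for the decision rule. The recruitment criterion is a count that cannot separate uptake from volume, and nothing in Criteria for success tests the share of eligible patients recruited.

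The firmer half of the point needs no outside figure: at 70 a year the rule requires 69% uptake, and the planned 60% is expected to miss it by half a patient a month. Correcting the threshold alone would remove that contradiction but leave the rule tied to this centre's volume.

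The other half, lower uptake passing, is conditional on volumes above 70. The word conservative makes this possible, but the documents do not show that it will happen. The figures treat all referrals as eligible, as the forecast does; the 23% chance of passing also assumes Poisson accrual.

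**What to change.** In Criteria for success:

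1. Keep a monthly count, but set it consistently with the recruitment plan (about 3.5 a month), or revise the forecast so that the two agree.
2. Add beside it a criterion on enrolled patients divided by eligible patients on the screening log, with its 95% interval, judged against the 60% planning value. State in advance how the estimate and interval will be compared with 60%, since at about 53 eligible patients the interval spans roughly 46% to 74%.
3. Report eligible patients per month, so that other sites can combine the uptake estimate with their own volume.
4. Do not use a lower limit above 23% as the pass rule.

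The change is a sentence or two and needs no extra patients or data. Its downside is that the result depends on complete logging of eligible patients, which the screening procedure already requires.
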